### Procedures for selecting participants and randomization

Eligible patients in labor will be invited to participate and those who agree and sign the informed consent form will be included in the study and then will be allocated to either using furosemide or placebo according to a random list of numbers generated by the Random Allocation Software Ispharan Iran, version 1.0. This list of randomization will be provided by the statistician to the pharmacist who will be responsible for preparing the packages containing either the furosemide or placebo, both in an identical presentation, with the identification number of list labeled. This procedure will be followed in order to guarantee the concealment of allocation of patients in both arms. Both patients and medical staff should be blind of the intervention condition in each case. Study medication and placebo, after delivered by the pharmaceutical industry to the pharmacy, will be packed as previously described and according the random list. The pharmacy will be responsible for sending sets to the ICU were the nurse in charge will keep all the packages until the administration of the drug to the patient according to the patients’ enrollment. The subjects will receive the study medication every 24 hours for a maximum of five days.

During the observation period the women will be subject to strict control of blood pressure, urine output (diuresis evaluated spontaneous or urinary catheter) and weight control. The routine management adopted at the hospital will be followed and other hypertensive agents will be initiated and chose according to the attending clinician's discretion.

### Sample size calculation

The calculation of sample size was done in the online public domain software version 2.3 Openepi (Atlanta, GA). Were used as reference data found in clinical trial using furosemide versus placebo, in which they found an average systolic blood pressure of 142 mmHg and a standard deviation of 13 mmHg and 153 mmHg and a standard deviation of 19 mmHg, respectively. For a power of 90 % and a significance level of 5 %, 94 patients would be needed in both groups to highlight this difference. In anticipation of possible post-randomization losses added up to total 20 % of patients, resulting in 120 for the two groups.

### Variables

#### Independent variable:

Furosemide or placebo.

### Dependent variables

Daily maximum systolic blood pressure; daily maximum diastolic blood pressure; maximum average daily blood pressure; heart rate; frequency of very high blood pressure episodes; control of blood pressure; need for maintenance of antihypertensive therapy for blood pressure control; number of antihypertensive agents used to control blood pressure; time required for recovery of blood pressure; urinary output; length of hospital stay; adverse effects (polydipsia, headache, confusion, muscle aches, tetany, muscle weakness, heart rhythm disturbances, gastrointestinal symptoms); puerperal complications during hospitalization (acute pulmonary edema, hemorrhagic manifestations, imminent eclampsia, eclampsia, maternal death, shock, persistent edema.

### Main outcomes

Systolic blood pressure (SBP): Determined by the appearance of the first sound of Korotkoff. Continuous quantitative variable, expressed in millimeters of mercury (mmHg).Diastolic Blood Pressure (DBP): Determined by the appearance of the fifth Korotkoff sound. Continuous quantitative variable, expressed in millimeters of mercury (mmHg).Mean arterial pressure (MAP): The value of mean arterial pressure in mmHg. Will be calculated by the formula: systolic blood pressure (SBP) plus twice the diastolic blood pressure (DBP) divided by three, being represented by (+2PAD SBP)/3. Continuous quantitative variable, expressed in millimeters of mercury (mmHg).Heart rate: Refers to the number of heart beats per minute, measured at least four times daily.Frequency of very high blood episodes: Defined as the daily number of very high blood pressure episodes, defined as Systolic blood pressure ≥ 180 mmHg or Diastolic blood pressure ≥ 110 mmHg.Control of blood pressure: Defined < 140 mmHg of systolic blood pressure and < 90 mmHg of diastolic blood pressure at all measurements (at least four) for a minimum 24-hour.Need for maintenance of antihypertensive therapy for blood pressure control: Use of anti-hypertensive agents for blood pressure control.Number of antihypertensive agents used to control blood pressure: Number of antihypertensive agents used to control blood pressure.Time required for recovery of blood pressure: Time to achieve control of blood pressure expressed in whole numbers.Hospital stay: For time elapsed between the beginning of inpatient treatment with furosemide or placebo until discharge.Daily urine output: Defined as the average amount of urine excreted, expressed in milliliters (ml), collected by probe or spontaneous voiding during hospitalization.

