Besides the mobilization of liquid from the interstiticial and intravascular to extravascular space corresponding to six to eight liters of the total body water, there is also a return of 950 mEq of total body sodium accumulated during pregnancy. It is observed increased urinary sodium excretion between three and five days after birth [21] possibly due to the increase of atrial natriuretic peptide in the first week after delivery, which has a role in natriuresis and entails inhibition of aldosterone, angiotensin II and vasopressin [22]. Several approaches have been proposed to accelerate the postpartum maternal recovery, but the effectiveness of these approaches as well as the ideal antihypertensive treatment in the postpartum period, remain to be established. Furosemide use has been proposed with this goal. Patients with preeclampsia and eclampsia may experience persistent hypertension after delivery, in response to the mobilization of interstitial and extravascular fluid into the intravascular space, the excess of total body water and inadequate secretion of sodium due to reduced glomerular filtration [23]. This is an important rationale for furosemide therapy since by its mechanism of action, this loop diuretic can act in patients with fluid overload, eliminating the intravascular fluid that has been mobilized in the postpartum period and thereby reducing blood volume and blood pressure and also reducing the need of antihypertensive therapy [23]. This therapy is logical when considering the pathophysiology of postpartum hypertension, with the objective of maintain a low central venous pressure and pulmonary capillary wedge pressures, raising colloid osmotic pressure and preventing the development of pulmonary edema and congestive heart failure [24].

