### Main hypothesis

In women randomized to postpartum oral furosemide, in comparison to placebo:Daily averages of systolic, diastolic and mean arterial pressure (MAP) are lower, heart rate is the same and the frequency of very high blood pressure episodes is lower.Control of blood pressure is obtained earlier;Frequency of use of antihypertensive agent for the treatment of hypertensive crisis is lower, as well as the need for maintenance of antihypertensive therapy for blood pressure control;Fewer antihypertensive agents are needed in order to control blood pressure at hospital discharge;Time until blood pressure control is lower;Daily urine output is higher;Reduction of edema is obtained in less time;Length of hospital stay is reduced.

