### Eligibility criteria

Postpartum women diagnosed with severe preeclampsia, after completion of therapy with magnesium sulfate, with spontaneous diuresis and greater than 50 ml/h. Women with superimposed preeclampsia, or that used diuretics before admission to the intensive care unit (ICU), with acute or chronic kidney disease, diabetes mellitus; collagen disease; sickle cell anemia, patients with hemodynamic instability or with hypokalemia (K < 3.0 mEq/L) or patients with contraindications to the use of furosemide or unable to consent were excluded.

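### Daily urine output is averaged over the hospital stay rather than over fixed days from the first dose, so the averaging window can include off-treatment time and can differ between arms

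*Protocol article*

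**What the plan says.** Daily urine output appears under Secondary maternal outcomes. The Main hypothesis for furosemide against placebo is "Daily urine output is higher". Main outcomes then gives the definition: "Defined as the average amount of urine excreted, expressed in milliliters (ml), collected by probe or spontaneous voiding during hospitalization". It states no first day, no last day and no per-24-hour unit.

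Four other statements bear on the window:

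- Dosing (Procedures for selecting participants and randomization): "The subjects will receive the study medication every 24 hours for a maximum of five days".
- Monitoring (same section): "During the observation period the women will be subject to strict control of blood pressure, urine output". The start and end of that observation period are not given.
- Start of treatment (Eligibility criteria): women enter "after completion of therapy with magnesium sulfate, with spontaneous diuresis and greater than 50 ml/h", so some inpatient time precedes the first dose.
- Hospital stay (Main outcomes): the "time elapsed between the beginning of inpatient treatment with furosemide or placebo until discharge". The Main hypothesis for it is "Length of hospital stay is reduced".

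The Introduction also describes "increased urinary sodium excretion between three and five days after birth".

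**The concern.** The label promises a daily quantity, but the definition gives one average whose window is set by the hospital stay. Two problems can follow.

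1. Time off study drug may enter the average: days after the last dose and, on one reading, time before the first.
2. The window closes at discharge. That happens after randomization, and the trial itself expects treatment to change it. If women on furosemide go home sooner, their averages cover different postpartum days from those of women on placebo. The Introduction says that sodium excretion is not constant over those days.

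Diuresis is the mechanism offered for the hoped-for fall in blood pressure, so urine output is the outcome closest to that mechanism and would help to interpret either a positive or a null blood pressure result. A comparison over unequal windows weakens that use.

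**Working it through.** **The plan's own figure.** The article states no number for urine output. Its sample size rests on systolic pressure: 142 (SD 13) against 153 (SD 19) mmHg, power 90 %, two-sided 5 %.

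- Pooled variance = (13² + 19²)/2 = 265, so SD = 16.28.
- n per arm = 2 × 265 × (1.960 + 1.282)² / 11² = 46.02, rounded up to 47, or 94 in total.

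This agrees with the article. It does not test the present point. It is used below only as a convenient number per arm.

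**Step 1: which windows fit the text?**

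| Window | Off-treatment time included? | Length varies with discharge? |
|---|---|---|
| Admission to discharge | Before the first dose, and after the last dose if the stay continues | Yes |
| First dose to discharge | Only if the stay outlasts dosing | Yes |

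On both readings the window ends at discharge.

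**Step 2: effect of averaging in untreated days.** Assumptions: five treated days, the full effect on each of them, no effect on other days, and an unchanged SD of the average. None of these is in the article. The share of the daily difference retained is f = 5 / (5 + u), where u is the number of untreated days averaged in. For power, take a standardized treated-day effect d = 0.669, chosen to give 90 % power at 47 per arm. Then power = Φ(d × f × √(47/2) − 1.96).

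| u | f | Power |
|---|---|---|
| 0 | 100 % | 90 % |
| 1 | 83 % | 77 % |
| 2 | 71 % | 64 % |
| 3 | 62.5 % | 53 % |
| 5 | 50 % | 37 % |

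With fewer dosing days the share is lower for the same u. Three dosing days and two untreated days give 3/5 = 60 %.

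**Step 3: effect of unequal stays when the drug has no effect on urine.** Assume the same profile in both arms: 2.0, 2.5, 3, 3, 3, 2, 2, 2 L on days 1 to 8. The shape is invented for illustration. The Introduction speaks of sodium excretion, not urine volume.

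- 3-day stay: 7.5 / 3 = 2.50 L
- 5-day stay: 13.5 / 5 = 2.70 L
- 8-day stay: 19.5 / 8 = 2.44 L

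If furosemide shortened every stay from 5 to 3 days, its average would be lower by 0.20 L (2.50 against 2.70). If it shortened every stay from 8 to 5 days, its average would be higher by 0.26 L (2.70 against 2.44). Neither difference reflects any drug action on urine, and the two have opposite signs.

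**The case against.** A reader might infer more than this: that the average certainly includes labour and the magnesium sulfate period, that the comparison is therefore diluted, and that only 60 to 83 % of the effect survives. The article does not support that.

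- The definition next to this one counts hospital stay from the first study dose, and the objectives compare women already receiving furosemide or placebo postpartum. A window starting at the first dose is at least as natural a reading.
- The reference to hospitalization may describe where the urine is collected, and the label does say daily.
- The 60 to 83 % range comes from assuming one or two pre-dose days and three to five dosing days. With none averaged in, 100 % is retained.
- No stay longer than five days is stated. If averaging starts at the first dose and every stay ends within the dosing period, there is no dilution.
- Unequal stays can push the difference either way, so calling the error dilution would be wrong.

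These points stand and limit the claim. They do not remove it, because even the window from first dose to discharge varies between women and closes at an event that treatment may affect.

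It can also be said that a journal article leaves averaging rules to the full protocol. Here, however, the article does state a rule, and the rule as stated has this weakness.

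A last objection is that day-by-day reporting does not fully cure the problem, because later days contain only women not yet discharged. That is correct, and the fix has to allow for it.

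**Conclusion.** The point holds in limited form. As written, the definition of daily urine output is not anchored to the treatment period, can admit off-treatment time, and ends at discharge. The arms may be compared over different postpartum days, with error of unknown sign.

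The size cannot be derived from the article. Under the assumptions shown, retention runs from 100 % down to about 60 %, or lower if more untreated days are averaged in, and unequal stays can add a shift in either direction. This is a minor matter: the outcome is secondary and touches neither the sample size nor the primary outcomes. It is worth correcting because the present wording allows several windows and the correction is cheap.

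**What to change.** Replace the definition with 24-hour urine volume, in ml per 24 h, for each day counted from the first study dose. Make the main comparison over a fixed early window that is the same in both arms, for example the first 24-hour periods during which nearly all women are still inpatients. The article gives no stay lengths, so the number of periods should be set from the hospital's usual length of stay and written down before the groups are unmasked. Report the remaining days up to day five descriptively, with the number of women still in hospital in each arm on each day.

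The cost is a few sentences of text. Urine output is already monitored, so little or no extra collection is needed. The downside is that later days no longer form part of the main comparison.

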### Data collection procedures

#### Data collection

For data collection, a pre-coded standard form will be used for data entry on the computer. After identifying the patients who are according to the eligibility criteria, using a specific check list, and who agree to participate in the study and sign the informed consent form, information will be collected and filled in the form. The checklist, as well as the form will be completed by the researchers.

Upon completion, the forms will be rigorously reviewed by the researchers to cross-check the information collected with the information contained in the records. Procedures for quality control, such as reviewing the completed forms and check manually typing will be adopted. A first quality control of data collection should be done before and during the typing of electronic records, to identify possible inconsistencies in the data researcher. The second quality control will check the compatibility between the physical archived records and data contained in electronic forms. The data will be entered in a specific database, created using the Epi Info statistical program 7.1.4 or an updated version available at this time. Each month the database will be reviewed by the principal investigator, getting listing of variables and correcting any inconsistencies or missing information from the query to the forms.

### Data analysis plan

The data analysis will be performed using the public domain software Epi Info version 7.1.4 (Centers for Disease Control and Prevention, Atlanta, GA), or the newest available version at the time of analysis) under the intention to treat principle.

The statistician will remain blind to the meaning of the Groups A or B to which patients are allocated until the tables and the analysis concluded. The approach for analysis will be that showed in Fig. 1 using an intention-to-treat strategy and following the correspondent recommendations from the CONSORT statement [11].

**Fig. 1 Fig1:**
[figure not shown]
Study design and population (CONSORT, 2010) [27]

The characteristics of the participants in each group will be compared with Student’s *t* test for continuous variables with normal distribution and Mann–Whitney U test for discrete and ordinal variables or those with non-normal distribution. Categorical variables will be compared with Pearson’s χ [2] test or Fisher’s exact test, as appropriate. P values for all tests will be two tailed at a 5 % level of significance.

Risk ratios and their 95 % confidence intervals will be calculated as a measure of relative risk. The number needed to treat (NNT) and its 95 % confidence interval will be calculated for the outcomes in which a beneficial effect of using furosemide is achieved, using the EBM calculator [http://moosenose.com/EBCalculator.htm]; in case of adverse effects the number needed to harm (NNH) and its 95 % confidence will also be calculated.

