In the systematic Cochrane Review that evaluated prevention and treatment of postpartum hypertension were included nine randomized clinical trials, of which two trials (282 women included) assessed postnatal furosemide at a dosage of 20-40 mg orally daily), compared with placebo or no treatment [25]. One trial added potassium supplementation (20 mEq orally daily) [23] and in the other [26] women at “high risk” of eclampsia also received magnesium sulfate. None of the studies reported the mean and standard deviation of the baseline blood pressure but one trial [26] reported a greater decrease in blood pressure in the group receiving furosemide compared to placebo. In the group receiving furosemide it was reported a change of blood pressure on days one, three and seven after delivery (i.e., −6.5 mmHg (furosemide) versus −3.5 (placebo) on day one, −10.6 (furosemide) versus −9.75 (placebo) on day three, and −11.5 (furosemide) versus −7.8 (placebo) on day seven). In the other trial [23] including 264 women, only postpartum patients with severe preeclampsia (*n* = 70) who received furosemide compared with controls had significantly lower systolic blood pressure by postpartum day 2 (142 +/− 13 mmHg compared with 153+/−19 mmHg, *P* < .004) and required less antihypertensive therapy during hospitalization (14 % compared with 26 %, *p* = 0.371) and at discharge (6 % compared with 26 %, *P* = 0.045). Follow-up ranged from day 10 postpartum [23] to six weeks postpartum [26].

The reviewers conclude that reliable data are not available to guide management of women with postpartum hypertension. For women with pre-eclampsia, postnatal furosemide may decrease the need for postnatal antihypertensive therapy in hospital, but more data are needed on substantive outcomes before this practice can be recommended. Notwithstanding, the optimal management of postpartum hypertension is not yet well established.

Thus, to determine the potential benefit of using diuretics in women with preeclampsia is an important issue in modern obstetrics. This study will be carried out with the objective of determining the effectiveness of furosemide to accelerate the recovery of hypertension in postpartum patients with severe preeclampsia.

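### Daily blood pressure is compared by unadjusted two-sample tests that make no use of pre-dose pressure: a loss of precision and of protection against chance imbalance, not a validity error

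*Protocol article*

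**What the plan says.** The Data analysis plan (text after the Fig. 1 caption) holds the document's only list of between-group tests. Continuous variables get Student's t "test for continuous variables with normal distribution and Mann–Whitney U test for discrete and ordinal variables or those with non-normal distribution", and categorical variables get Pearson's chi-square or Fisher's exact test. It adds that "P values for all tests will be two tailed at a 5 % level of significance". Risk ratios, NNT and NNH complete the list. No regression model, covariate or change from baseline appears anywhere in the article.

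The primary outcomes include daily averages of systolic, diastolic and mean arterial pressure, all measured after treatment starts. The section on selection and randomization describes a computer-generated random list and no stratification by blood pressure.

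The Sample size calculation treats systolic pressure as an unadjusted comparison of two means. The reference trial is cited for furosemide ("they found an average systolic blood pressure of 142 mmHg and a standard deviation of 13 mmHg") and for placebo ("153 mmHg and a standard deviation of 19 mmHg, respectively"), and the result is: "For a power of 90 % and a significance level of 5 %, 94 patients would be needed in both groups".

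Two other places bear on baseline pressure. The Introduction says of the earlier furosemide trials: "None of the studies reported the mean and standard deviation of the baseline blood pressure". The randomization section says that during the observation period "the women will be subject to strict control of blood pressure". Neither names a pre-dose reading as a study variable.

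**The concern.** A woman's pressure shortly before the first dose may be expected to predict her pressure over the following days, although the documents do not say how strongly. With a plain two-sample test, that predictable part of the variation stays in the error term and widens the confidence interval.

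A chance difference between arms in starting pressure also passes into the estimated effect in proportion to the correlation. About 47 to 60 women per arm and no described stratification make chance differences of a few mmHg ordinary. At stake are the width of the interval and how convincing the result is if the arms happen to start apart. Adjustment needs no extra patients, and it has to be chosen before the imbalance is seen.

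**Working it through.** **Inputs from the protocol.** SDs 13 and 19 mmHg, means 142 and 153 (difference 11), power 90 %, two-sided 5 %, 94 women in total (Sample size calculation and Data analysis plan).

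**Assumptions.** Allocation is 1:1 (no ratio is stated, but 94 is reproduced as 47 + 47). The correlation r between pre-dose and post-dose pressure is 0.3 to 0.7 (not in the documents). For the imbalance figures, the baseline SD equals the outcome SD.

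**Step 1: reproduce the plan's figure.**
n per arm = (13² + 19²)(1.960 + 1.282)² / 11² = 46.02, rounded up to 47, so 94 in total. It agrees. Allowing 20 % loss, 94 / 0.8 = 117.5, close to the stated 120.

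**Step 2: the unadjusted comparison.**
- Root-mean-square SD = √((169 + 361)/2) = 16.28 mmHg.
- Standard error at 47 per arm = 16.28 × √(2/47) = 3.36 mmHg.
- 95 % CI half-width = 1.96 × 3.36 = 6.6 mmHg.
- Power at 11 mmHg = 90.6 % (95.9 % if all 60 per arm are evaluable).

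**Step 3: ANCOVA on pre-dose pressure.** The residual SD is 16.28 × √(1 − r²), and the equivalent unadjusted sample is 94 / (1 − r²).

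| r | SE multiplier | Residual SD (mmHg) | CI half-width (mmHg) | Power at 11 mmHg | 94 women worth |
|---|---|---|---|---|---|
| 0 (as planned) | 1 | 16.28 | 6.6 | 90.6 % | 94 |
| 0.3 | 0.95 | 15.53 | 6.3 | 93.0 % | 103 |
| 0.5 | 0.87 | 14.10 | 5.7 | 96.6 % | 125 |
| 0.7 | 0.71 | 11.63 | 4.7 | 99.6 % | 184 |

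The document gives planning SDs for systolic pressure only. The SE multiplier depends on r alone, so it carries over to diastolic and mean arterial pressure at the same r.

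**Step 4: chance imbalance.** With equal SDs the baseline difference between arms also has a standard error of 3.36 mmHg, and the shift in the unadjusted estimate is r × gap.
- Gap of 4 mmHg: 4 / 3.36 = 1.19 standard errors, reached in either direction in about 23 % of trials. Shift at r = 0.5: 0.5 × 4 = 2.0 mmHg (1.2 at r = 0.3, 2.8 at r = 0.7).
- Gap of 6.6 mmHg (1.96 standard errors, about 1 trial in 20): shift of 2.0, 3.3 or 4.6 mmHg at r = 0.3, 0.5 or 0.7.

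Given a baseline gap of k standard errors, the type I error is 1 − Φ((1.96 − rk)/√(1 − r²)) + Φ((−1.96 − rk)/√(1 − r²)). At k = 1.96 it is about 8 %, 13 % and 21 % for r = 0.3, 0.5 and 0.7. At k = 1 it is 5.0 %, 4.8 % and 3.9 %. Only the larger gaps inflate it, and over all randomizations it averages to 5 %.

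**The case against.** The strongest reply is that nothing planned fails. A t test on post-treatment means in a randomized trial is valid, the sample size was computed for that same comparison, and it reproduces with the intended power. This stands, and it limits the point to precision and robustness.

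Second, covariate adjustment is often settled in a statistical analysis plan, and the literal subject of the test sentence is participant characteristics, which could mean baseline only. But it is the only test list, its significance level covers all tests, and the sample size rests on the same unadjusted comparison. Read as the outcome analysis, it states an unadjusted method. Read as baseline only, the article names no test for the primary outcome.

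Third, the gain depends on an unknown correlation. Clinicians may add antihypertensives at their discretion, and treatment that follows pressure could weaken the correlation, especially on later days. This stands too: at r = 0.3 the gain is slight. A smaller true effect makes the gain look larger. At 8 mmHg and 47 per arm, for instance, power goes from 66 % to 79 % at r = 0.5. But 8 mmHg is not a protocol figure, and with 60 per arm the unadjusted power there is already about 77 %.

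A reader might infer three stronger points that the documents do not support:
- **That unequal planning SDs undermine Student's t.** With SDs 13 and 19 and 47 per arm its type I error is 4.9 %. It reaches about 6.2 % only with a split such as 54/40 and the smaller SD in the larger arm, which the protocol does not describe. This is no reason for change.
- **That the pre-dose reading is already recorded.** ICU care and at least four daily measurements for the control outcome make one very likely, but no section names it.
- **That the Introduction faults earlier trials for neglecting baseline pressure.** It only reports that those figures were not given.

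**Conclusion.** The point holds as an efficiency and robustness improvement that should be made; it is not an error that threatens the trial's validity. Under the protocol's own inputs the unadjusted analysis has a 5 % error rate and about 90 % power.

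Baseline adjustment would narrow the interval by 5 % to 29 % for r between 0.3 and 0.7. It would also remove a shift of about 2 mmHg when the arms start 4 mmHg apart (r = 0.5, equal SDs), against a planned effect of 11 mmHg. The range of r and the equality of SDs are assumptions. The absence of any baseline term is plain from the text.

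**What to change.** Before unblinding, pre-specify ANCOVA for systolic, diastolic and mean arterial pressure, with arm and the last pre-dose value of the same measure as covariate. Report the adjusted mean difference with its 95 % CI. Define the pre-dose reading, for example as the last one before the first dose, and make it a required field on the data form. Keep the sample size as it is.

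The cost is a few lines of analysis wording and at most one form field. No extra patients are needed and patient care does not change. The Data analysis plan names Epi Info, so confirm that it can fit this model, or name other software for this analysis.

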### Secondary maternal outcomes

Control of blood pressure;Frequency of use of antihypertensive agent for the treatment of hypertensive crisis;Need for maintenance of antihypertensive therapy for blood pressure control;Number of antihypertensive agents used to control blood pressure at hospital discharge;Time until blood pressure control;Daily urine output;Reduction of edema;Length of hospital stay;Adverse effects: hypokalemia, polydipsia, headaches, mental confusion, muscle aches, tetany, muscle weakness, heart rhythm disturbances and gastrointestinal symptoms;Frequency of maternal complications: imminent eclampsia, eclampsia, infection, bleeding manifestations, shock and maternal death.

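### NNH is the only absolute measure planned for adverse effects; at about 60 women per arm its interval will often run through infinity, so a risk difference with a score-type interval should be reported instead

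*Protocol article*

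**What the plan says.** The protocol article's data analysis plan (the text after Fig. 1) compares categorical variables with Pearson's chi-square or Fisher's exact test, two-tailed at 5 %. The effect measures for binary outcomes are then:

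- Relative: "Risk ratios and their 95 % confidence intervals will be calculated as a measure of relative risk".
- Absolute, benefit: NNT with a 95 % interval, limited to outcomes where furosemide turns out beneficial.
- Absolute, harm: "in case of adverse effects the number needed to harm (NNH) and its 95 % confidence will also be calculated".

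No risk difference is named. The secondary maternal outcomes hold two separate safety lists. One is adverse effects, such as hypokalemia, headaches and muscle weakness. The other is maternal complications: "imminent eclampsia, eclampsia, infection, bleeding manifestations, shock and maternal death". Expected event rates are given for neither list. Under the sample size heading, "94 patients would be needed in both groups to highlight this difference", raised for losses, "resulting in 120 for the two groups".

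**The concern.** NNH is the reciprocal of the risk difference. When the interval for the risk difference includes zero, inverting its two limits gives one negative and one positive number, and the range between them does not contain the estimate. The true interval is in two pieces that meet at infinity. Unless that is recognised, the safety table can show a range that excludes its own estimate.

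The risk ratio fills the gap only in part. It is a relative measure, and its usual log-based interval does not exist when an arm has no events. At stake is whether a reader can see how much harm the trial leaves open. For example, 0 of 60 is still compatible with a risk of about 6 %.

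**Working it through.** **Inputs.** From the article's sample size section: systolic means and SDs of 142 (13) and 153 (19) mmHg, 90 % power, 5 % significance, 94 women before losses and 120 after. The arm size of 60 assumes 1:1 allocation, which the article implies but does not state. All event rates below are assumptions.

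**1. The plan's own figure.** n per arm = (13² + 19²)(1.960 + 1.282)² / 11² = 46.02, so 47 per arm and 94 in total, as stated. Allowing for 20 % losses, 94 / 0.80 = 117.5, so 118, close to the stated 120. Arm sizes are therefore about 60, or about 47 if the losses occur.

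**2. One worked table, 5/60 v 2/60.**
- Risk difference = 0.0833 − 0.0333 = 0.050, so NNH = 1/0.050 = 20.
- SE = √(0.0833 × 0.9167/60 + 0.0333 × 0.9667/60) = 0.0425.
- Wald 95 % interval = 0.050 ± 1.96 × 0.0425 = −3.3 to 13.3 points.
- Inverted limits: −29.9 and 7.5. The estimate of 20 does not lie between them.
- Correct form: NNH 7.5 to infinity to NNT 29.9.

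**3. How often the risk-difference interval includes zero.** This is an exact sum of the binomial probabilities over all pairs of counts.

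| Assumed true rates | 60 per arm: Wald / Newcombe | 47 per arm: Wald / Newcombe |
|---|---|---|
| 5 % v 2 % | 86 % / 93 % | 91 % / 96 % |
| 5 % v 5 % | 94 % / 97 % | 95 % / 98 % |
| 10 % v 5 % | 80 % / 86 % | 83 % / 90 % |
| 20 % v 10 % | 64 % / 68 % | 71 % / 75 % |
| 30 % v 10 % | 19 % / 21 % | 28 % / 31 % |

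With Newcombe's method at 60 per arm, a finite NNH interval needs at least 5 v 0, 7 v 1, 10 v 3, 15 v 6 or 22 v 12 events.

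**4. How often the log risk-ratio interval fails.** P(at least one arm has no event) = 1 − [1 − (1 − p)^60]², with the same rate p in both arms:
- 1 %: 1 − (1 − 0.547)² = 79 %
- 2 %: 51 %
- 5 %: 9 %
- 10 %: 0.4 %

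Both arms are empty in 30 % of trials at 1 % and in 9 % at 2 %. With 47 per arm, at least one arm is empty in 86 % at 1 % and in 62 % at 2 %.

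**5. What a risk difference gives in the same tables.** Newcombe's interval is always finite:
- 6/60 v 3/60: 5.0 points (−5.2 to 15.7)
- 2/60 v 0/60: 3.3 points (−3.2 to 11.4)
- 0/60 v 0/60: 0 points (−6.0 to +6.0), since the Wilson upper limit for 0/60 is 1.96²/(60 + 1.96²) = 6.0 %

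The exact upper limit for a single arm with 0/60 is 1 − 0.025^(1/60) = 6.0 %.

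**The case against.** The strongest reply is that the article contains no wrong interval. It names no formula, no way of printing the interval and no treatment of empty cells, and such detail is commonly left to a fuller document. The NNH clause follows an NNT rule limited to achieved benefit, so it can be read in parallel as applying only where harm is shown; the interval would then normally be finite. Fisher's exact test is planned for sparse tables, CONSORT reporting is promised, and a reader given counts could derive the limits.

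Much of this stands, and it rules out several stronger readings that a reader might infer:
- **That NNH is required whatever the result.** The clause does not say so; its scope is unclear.
- **That the safety intervals are wrong or absent.** An interval through infinity has a correct notation. It is wrong only if inverted limits are printed as an ordinary range, and nothing says they will be.
- **That the risk ratio cannot be computed for rare events.** The log interval fails only with an empty cell. With one empty arm, score or exact methods still give a bound; only 0 v 0 has no estimate.
- **That most harm comparisons are affected.** This depends on rates the article does not give, and at 30 % v 10 % it is untrue.
- **That eclampsia, shock and death illustrate the NNH problem.** They are on the complications list, whereas the NNH clause names adverse effects. They bear on the risk ratio.

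What does not stand is that nothing is left. The choice of absolute measure is stated, not omitted. An unrestricted NNH will often have a discontinuous interval. An NNH restricted to demonstrated harm leaves the other harms with no absolute estimate. Fisher's test supplies a P value, not the size of the harm that remains possible.

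**Conclusion.** The point holds as a minor one. NNH is a poor choice as the sole absolute measure of harm at this sample size, under either reading of the clause. With about 60 per arm, the risk-difference interval includes zero in 80 to 86 % of trials at 10 % v 5 % and in 64 to 68 % at 20 % v 10 %, falling to 19 to 21 % at 30 % v 10 %. The risk ratio's usual interval is lost in about 79 % of trials at a true 1 % rate and 51 % at 2 %, but in only 9 % at 5 %, so that part matters mainly for rare complications. These figures rest on assumed event rates and 1:1 allocation; losses make them somewhat worse. The primary analysis, the tests and the sample size are unaffected.

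**What to change.** In the data analysis plan, replace the NNH clause with a rule for both safety lists:

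1. For each adverse effect and each maternal complication, report events/n per arm and the risk difference (furosemide minus placebo) with a Newcombe or other score-type 95 % interval.
2. Give NNH only as a supplement, either when that interval excludes zero or in the form NNH x to infinity to NNT y.
3. Keep the risk ratio with its 95 % interval where both arms have events.

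The cost is a few sentences and a different interval formula. No new data are needed. The change is best made before the treatment groups are unmasked.
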